|  | **Instruction for data collectors on LIKERT scales:**  In this section, the 2 step approach needs to be used:  **Give SHOWCARD 7 to the participant to help them through the responses**  Ask the question in two parts:   1. Ask the participant the specific question as written below 🡪Participant answers: Yes/neutral/no   Data collector asks: ‘do you strongly or moderately (dis)agree’ | | inst_psa1 |
|  | Intro: **We want to explore how you feel about having pre-diabetes / diabetes. Please respond in relation to the condition you have, i.e. either diabetes or pre-diabetes using the options provided.** | | |
| A | Do you think that pre-diabetes / diabetes is the worst thing that has ever happened to you?  1 Strongly disagree  2 Disagree  3 Neutral  4 Agree  5 Strongly agree  888 Not applicable | └──┘ | PSA_1a |
| B | Do you often feel embarrassed about having pre-diabetes / diabetes?  1 Strongly disagree  2 Disagree  3 Neutral  4 Agree  5 Strongly agree  888 Not applicable | └──┘ | PSA_1b |
| C | Do you think there is little hope of leading a normal life with pre-diabetes / diabetes?  1 Strongly disagree  2 Disagree  3 Neutral  4 Agree  5 Strongly agree  888 Not applicable | └──┘ | PSA_1c |
| D | Do you think the proper control of pre-diabetes / diabetes involves a lot of sacrifice and inconvenience?  1 Strongly disagree  2 Disagree  3 Neutral  4 Agree  5 Strongly agree  888 Not applicable | └──┘ | PSA_1d |
| E | Do you try not to let people know about your pre-diabetes / diabetes?  1 Strongly disagree  2 Disagree  3 Neutral  4 Agree  5 Strongly agree  888 Not applicable | └──┘ | PSA_1e |
| F | Do you think pre-diabetes / diabetes is not really a problem because it can be controlled?  1 Strongly disagree  2 Disagree  3 Neutral  4 Agree  5 Strongly agree  888 Not applicable | └──┘ | PSA_1f |

| **SECTION 18: TREATMENT SATISFACTION** | | | | |
| --- | --- | --- | --- | --- |
| **Instruction for data collectors on LIKERT scales:**  In this section, the 2 step approach needs to be used:  **Give SHOWCARD 7 to the participant to help them through the responses**  Ask the question in two parts:   1. Ask the participant the specific question as written below 🡪Participant answers: Yes/neutral/no   Data collector asks: ‘do you strongly or moderately (dis)agree’ | | | | inst_ts1 |
| The following question relates to your experience regarding the treatment and follow-up of your **diabetes / pre-diabetes** | | | | |
| **S.NO:** | **Questions** | **Response** | **Code** | |
| A | Are you satisfied with the services you received at the health center?  1 Strongly disagree  2 Disagree  3 Neutral  4 Agree  5 Strongly agree  888 Not applicable | **└──┘** | TS_1a | |

| **SECTION 19: QUALITY OF LIFE & STRESS** | | | |
| --- | --- | --- | --- |
| **S.NO:** | **Questions** | **Response** | **Code** |
| A | At this point of time in your life, consider your home situation, relationships, finances, work situation and other aspects of your life, how would you describe the quality of your life overall?  Excellent = 1  Good = 2  Fair = 3  Poor = 4  Don’t know/neutral/unsure = 777 | **└──┘** | QOL_1a |
| B | Which of these best describe your health?  Excellent = 1  Good = 2  Fair = 3  Poor = 4  Don’t know/neutral/unsure = 777 | **└──┘** | QOL_1b |
| C | 1. Are you currently facing any serious on-going problems that affects your health?  Yes = 1  No = 0  **If NO, SKIP to D** | **└──┘** | QOL_1c1 |
|  | 2. If YES, would you say this problem has been…  1 = Not very stressful  2 = Moderately stressful  3 = Very stressful | **└──┘** | QOL_1c2 |
|  | 3. Has this been a problem for 12 months or more?  Yes = 1  No = 0 | **└──┘** | QOL_1c3 |
| D | 1. Are you currently facing any serious on-going problem that affects your job or ability to work (including housework)?  Yes = 1  No = 0  **IF NO, SKIP to E** | **└──┘** | QOL_1d1 |
|  | 2. If YES, would you say this problem has been…  1 = Not very stressful  2 = Moderately stressful  3 = Very stressful | **└──┘** | QOL_1d2 |
|  | 3. Has this been a problem for 12 months or more?  Yes = 1  No = 0 | **└──┘** | QOL_1d3 |
| E | 1. Are you currently facing any on-going financial strain/stress or difficulties?  Yes = 1  No = 0 | **└──┘** | QOL_1e1 |
|  | 2. If YES, would you say this problem has been…  1 = Not very stressful  2 = Moderately stressful  3 = Very stressful | **└──┘** | QOL_1e2 |
|  | 3. Has this been a problem for 12 months or more?  Yes = 1  No = 0 | **└──┘** | QOL_1e3 |
| F | Are you currently facing any on-going difficulties in a relationship with someone close to you?  Yes = 1  No = 0 | **└──┘** | QOL_1f1 |
|  | 2. If YES, would you say this problem has been…  1 = Not very stressful  2 = Moderately stressful  3 = Very stressful | **└──┘** | QOL_1f2 |
|  | 3. Has this been a problem for 12 months or more?  Yes = 1  No = 0 | **└──┘** | QOL_1f3 |
|  | **Do any of the following currently cause stress in your life?**  ~~1 Yes~~  ~~2 No~~  ~~3 Don’t know~~ | |  |
| ~~L~~ G | Social isolation  1 Yes  0 No  777 Don’t know | **└──┘** | QOL_1g |
| ~~M~~ H | Lack of education  1 Yes  0 No  777 Don’t know | **└──┘** | QOL_1h |
| ~~N~~ I | Unemployment  1 Yes  0 No  777 Don’t know | **└──┘** | QOL_1i |
| ~~O~~ J | Family problems  1 Yes  0 No  777 Don’t know | **└──┘** | QOL_1j |
| ~~P~~ K | Marriage/Relationships  1 Yes  0 No  777 Don’t know | **└──┘** | QOL_1k |

| **SECTION 20: KNOWLEDGE ABOUT DIABETES** | | | |
| --- | --- | --- | --- |
| **S.No.** | **Questions** | **Response** | **Code** |
| A | If someone has diabetes, that persons’ children have a higher chance of getting diabetes  1 Yes  0 No  777 Don’t know | └──┘ | KNOW_1a |
| B | Regular exercise will decrease the need for insulin or other diabetic medication  1 Yes  0 No  777 Don’t know | └──┘ | KNOW_1b |
| C | People with diabetes should take extra care when cutting their toenails  1 Yes  0 No  777 Don’t know | └──┘ | KNOW_1c |
| D | Diabetes can cause loss of feeling in my hands, fingers and feet  1 Yes  0 No  777 Don’t know | └──┘ | KNOW_1d |
| E | A diabetic diet consists mostly of special foods which are difficult to obtain  1 Yes  0 No  777 Don’t know | └──┘ | KNOW_1e |
| F | Diabetes can damage the kidneys  1 Yes  0 No  777 Don’t know | └──┘ | KNOW_1f |
| G | Frequent urination and thirst are typical signs of low blood sugar  1 Yes  0 No  777 Don’t know | └──┘ | KNOW_1g |
| H | Diabetes is a disease that requires lifelong treatment  1 Yes  0 No  777 Don’t know | └──┘ | KNOW_1h |
| I | Taking medication against diabetes is only useful when you have symptoms  1 Yes  0 No  777 Don’t know | └──┘ | KNOW_1i |
| J | Overweight may cause diabetes  1 Yes  0 No  777 Don’t know | └──┘ | KNOW_1j |
| K | An person with uncontrolled diabetes has a higher risk to suffer from a heart disease or a stroke  1 Yes  0 No  777 Don’t know | └──┘ | KNOW_1k |

**For participants with PRE-DIABETES, END HERE!**

PART III: Selected context measures

Context is multi-layered and highly complex, including micro- and macro-components stretching from individual attitudes and beliefs to the wider socio-political climate. We will attempt to measure only those aspects of context which are relevant to the implementation of SMART2D and thereby the outcome as well. The conceptual figure shown below has been modified from Taplin et al and attempts to describe the most relevant layers for SMART2D and the aspects that will be measured using quantitative data collection tools. Figure 2 shows each aspect that will the measured and the corresponding tools *(in italics)*. The grey circles represent areas not covered by these evaluation tools. Some aspects such as lay support networks have been studied to some extent in the formative part and others such as socio-political climate of each setting will be mainly described using narratives to keep track of temporal changes.

*Figure 2: Context measures and corresponding tools*

*
[figure not shown]
*

**Table 3: Details of tools, sources and data collection points for Part III**

| Questionnaires | Source | BL | M2-11 | EL |
| --- | --- | --- | --- | --- |
| **Out of pocket expenditure: Individual and family questionnaire** | Prepared by [name] | X |  | X |
| **Health facility survey – to be administered to head of health facility*** | Prepared by [name] |  | X |  |
| **EPOCH – to be conducted by researcher and collected one per community*** | Environmental Profile of a Community’s Health (Clara Chow – Population Health Research Institute, Hamilton) |  | X |  |

* Not included in this set of data collection tools

| **SECTION 21: Out of Pocket Expenditure related to type 2 diabetes** | | | |
| --- | --- | --- | --- |
| **SECTION 21A: Out of Pocket Expenditure – Outpatient cost** | | | |
| **S.NO:** | **Questions** | **Response** | **Code** |
| A | Do you usually spend any money on medication and other related costs? | 1 Yes regularly  2 Yes occasionally  0 No  **If NO, SKIP to B** | OOPO_1a |
|  | **In the last month, how much did you spend on the following items in relation to treatment of type 2 diabetes?**  *Please record in respective local currency for each setting: Ug Sh (Uganda)/SAR (South Africa)/SEK (Sweden)* | | |
| B | Medicine:  1. Diabetes medication  2. Other medication | 1. └─┴─┴─┴─┴─┴─┴─┘  2. └─┴─┴─┴─┴─┴─┴─┘ | OOPO_1b1  OOPO_1b2 |
| C | Consultation fees  Not applicable = 888 | └─┴─┴─┴─┴─┴─┴─┘  └──┴──┘ | OOPO_1c |
| D | Laboratory tests  Not applicable = 888 | └─┴─┴─┴─┴─┴─┴─┘  └──┴──┘ | OOPO_1d |
| E | Other supplies  Not applicable = 888 | └─┴─┴─┴─┴─┴─┴─┘  └──┴──┘ | OOPO_1e |
| F | Food while at the health facility  Not applicable = 888 | └─┴─┴─┴─┴─┴─┴─┘  └──┴──┘ | OOPO_1f |
| G | Appreciation of health worker  Not applicable = 888 | └─┴─┴─┴─┴─┴─┴─┘  └──┴──┘ | OOPO_1g |
| H | Transport ( to and from facility)  Not applicable = 888 | └──┴──┘ |  |

O

| **SECTION 21B: Out of Pocket Expenditure – Hospitalisation cost** | | | | | |
| --- | --- | --- | --- | --- | --- |
| I | In the past 12 months, how many times were you hospitalized ? | Number of times └─┴**─┘**  **If 0 SKIP to SECTION 21C** | | | OOPI_1i |
| **For each hospitalization** (max 3 – if more, take last 3) can you answer the following questions | | | | | inst_oopi1 |
|  |  | **1** | **2** | **3** |  |
| J | What was the reason for the hospitalization? | 1. Related to diabetes 2. Unrelated to diabetes   777. I don’t know | 1. Related to diabetes 2. Unrelated to diabetes   777. I don’t know | 1. Related to diabetes 2. Unrelated to diabetes   777. I don’t know | OOPI_1j1  OOPI_1j2  OOPI_1j3 |
| K | How many days were you hospitalised ? | **└──┘** | **└──┘** | **└──┘** | OOPI_1k1  OOPI_1k2  OOPI_1k3 |
| L | What was the total cost of your stay in the hospital? | └─┴─┴─┴─┴─┴─┴─┘ | └─┴─┴─┴─┴─┴─┴─┘ | └─┴─┴─┴─┴─┴─┴─┘ | OOPI_1l1  OOPI_1l2  OOPI_1l3 |
|  | Can you divide the costs for each hospitalisation into the following categories?  *Please record in respective local currency for each setting: Ug Sh (Uganda)/SAR (South Africa)/SEK (Sweden)* | | | | inst_oopi2 |
| M | Cost for medication while in the hospital | └─┴─┴─┴─┴─┴─┴─┘  777. I don’t know | └─┴─┴─┴─┴─┴─┴─┘  777. I don’t know | └─┴─┴─┴─┴─┴─┴─┘  777. I don’t know | OOPI_1m1 OOPI_1m2 OOPI_1m3 |
| N | Payment for accommodation | └─┴─┴─┴─┴─┴─┴─┘  777. I don’t know | └─┴─┴─┴─┴─┴─┴─┘  777. I don’t know | └─┴─┴─┴─┴─┴─┴─┘  777. I don’t know | OOPI_1n1  OOPI_1n2  OOPI_1n3 |
| O | Emergency room fees | └─┴─┴─┴─┴─┴─┴─┘  777. I don’t know | └─┴─┴─┴─┴─┴─┴─┘  777. I don’t know | └─┴─┴─┴─┴─┴─┴─┘  777. I don’t know | OOPI_1o1  OOPI_1o2  OOPI_1o3 |
| P | Consultation (doctor) fees | └─┴─┴─┴─┴─┴─┴─┘  777. I don’t know | └─┴─┴─┴─┴─┴─┴─┘  777. I don’t know | └─┴─┴─┴─┴─┴─┴─┘  777. I don’t know | OOPI_1p1  OOPI_1p2  OOPI_1p3 |
| Q | Surgery | └─┴─┴─┴─┴─┴─┴─┘  777. I don’t know | └─┴─┴─┴─┴─┴─┴─┘  777. I don’t know | └─┴─┴─┴─┴─┴─┴─┘  777. I don’t know | OOPI_1q1  OOPI_1q2  OOPI_1q3 |
| R | Supplies (bandages, syringes, catheters, etc) | └─┴─┴─┴─┴─┴─┴─┘  777. I don’t know | └─┴─┴─┴─┴─┴─┴─┘  777. I don’t know | └─┴─┴─┴─┴─┴─┴─┘  777. I don’t know | OOPI_1r1  OOPI_1r2  OOPI_1r3 |
| S | Laboratory test | └─┴─┴─┴─┴─┴─┴─┘  777. I don’t know | └─┴─┴─┴─┴─┴─┴─┘  777. I don’t know | └─┴─┴─┴─┴─┴─┴─┘  777. I don’t know | OOPI_1s1  OOPI_1s2  OOPI_1s3 |
| T | X-rays, scans etc | └─┴─┴─┴─┴─┴─┴─┘  777. I don’t know | └─┴─┴─┴─┴─┴─┴─┘  777. I don’t know | └─┴─┴─┴─┴─┴─┴─┘  777. I don’t know | OOPI_1t1  OOPI_1t2  OOPI_1t3 |
| U | My own food | └─┴─┴─┴─┴─┴─┴─┘  777. I don’t know | └─┴─┴─┴─┴─┴─┴─┘  777. I don’t know | └─┴─┴─┴─┴─┴─┴─┘  777. I don’t know | OOPI_1u1  OOPI_1u2  OOPI_1u3 |
| V | Ambulance/transport | └─┴─┴─┴─┴─┴─┴─┘  777. I don’t know | └─┴─┴─┴─┴─┴─┴─┘  777. I don’t know | └─┴─┴─┴─┴─┴─┴─┘  777. I don’t know | OOPI_1v1  OOPI_1v2  OOPI_1v3 |
| W | Cost for somebody accompanying me: accommodation | └─┴─┴─┴─┴─┴─┴─┘  777. I don’t know | └─┴─┴─┴─┴─┴─┴─┘  777. I don’t know | └─┴─┴─┴─┴─┴─┴─┘  777. I don’t know | OOPI_1w1  OOPI_1w2  OOPI_1w3 |

| **SECTION 21C: Household Expenditure** | | | |
| --- | --- | --- | --- |
| On average, how much did you spent in your household on the following in the LAST ONE MONTH?” Enter 777 if amount is not known.  *Please record in respective local currency for each setting: Ug Sh (Uganda)/SAR (South Africa)/SEK (Sweden)* | | | |
| A | Food, including such things as rice, meat, fruits, vegetables and cooking oil | └─┴─┴─┴─┴─┴─┴─┘ | HH_1a |
| B | Value of food consumed by the household which is produced/grown in the household | └─┴─┴─┴─┴─┴─┴─┘ | HH_1b |
| C | Gas, electricity, water, telephone and heating fuel | └─┴─┴─┴─┴─┴─┴─┘ | HH_1c |
| D | Transport, repair of vehicles | └─┴─┴─┴─┴─┴─┴─┘ | HH_1d |
| E | Housing rent. If house is not rented, ask about the rental value of patient’s house. | └─┴─┴─┴─┴─┴─┴─┘ | HH_1e |
| F | Education fees and supplies | └─┴─┴─┴─┴─┴─┴─┘ | HH_1f |
| G | Reimbursement of loans | └─┴─┴─┴─┴─┴─┴─┘ | HH_1g |
| H | Insurance premiums or prepaid health plans | └─┴─┴─┴─┴─┴─┴─┘ | HH_1h |
| I | Clothes, shoes and related items | └─┴─┴─┴─┴─┴─┴─┘ | HH_1i |
| J | Goods like washing machines, cooking utensils, stove, radio, furniture, bicycle | └─┴─┴─┴─┴─┴─┴─┘ | HH_1j |
| K | Special occasions including festivals, weddings, funerals, etc | └─┴─┴─┴─┴─┴─┴─┘ | HH_1k |
| L | Others | └─┴─┴─┴─┴─┴─┴─┘ | HH_1l |
| In addition to the above, have you spent any money in the LAST ONE YEAR on any special occasions in your family, illness of other members, purchase of house, car or other assets? 0 = No, 1 = Yes | | | |
| M | Specify |  | HH_1m |
| N | Specify |  | HH_1n |

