### 2.2.2 Secondary objectives

1. To determine the effect of the facility+ community strategies, in reducing the incidence of conversion from pre-diabetes state to diabetes state
2. To evaluate differences between the country sites, in regard to baseline context infrastructure situation for prevention and management of diabetes
3. To analyze the degree of implementation of the intervention elements in each country, and differences between the country sites, through a process evaluation at each site
4. To determine the effect of the interventions on: perceptions towards behavioral risk factors for diabetes; including physical activity and dietary behavior.

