### 3.3.2. Facility Strategies

#### 3.3.2.1 A generic model for the SMART2D Facility Intervention

To optimize and standardize facility care across the two arms (as well as across sites, to the extent possible), key common elements related to the organization of care process need to be in place in all the health facilities. SMART2D will review the present care, checking the implementation of the minimum level of quality care elements as outlined below in table 2. Should key elements be missing, they will be implemented as part of the trial.

*Facility Strategy I: Organization of the care process*

The first part of the facility strategy entails the optimization of the organization of the care process, which is divided into three components.

Firstly, ***minimal infrastructure*** should be ***adequate***, i.e. being in place and functional. Minimal basic equipment present at all facilities delivering care is: a glucometer and a sufficient amount of test strips, weighing scales, measuring tapes (for waist circumference), blood pressure machines (preferably electronic) and a stadiometer. Newly bought machines should have a certified quality brand, and all machines need to be calibrated following the quality procedures for medical equipment. A ***Quality Control Checklist*** will help to assure that adequate infrastructure is in place across all facilities in the trial.

Secondly, ***guidelines*** should be implemented. In case they do not exist, they will be developed, based upon internationally available guidelines for diabetes care and management, but adapted to the local context. The follow-up appointments with full clinical evaluation are proposed at month 6 and 12 (and 18?), but the frequency of doctor / nurse appointments will be contextualized to each setting based on need and current practice – e.g., patients with unstable glucose levels will need more frequent appointments. Three main entities depicted in the guidelines are: 1) ***a clinical guideline*** for medical practitioners; 2) ***a task-shifting guideline*** to map the organization of care, identifying level of staff, tasks and responsibilities, and shifting these to a lower level where appropriate; and 3) ***a patient flow chart***, identifying the steps in the care process from the patient’s perspective.

Thirdly, a ***patient health information system*** should be in place to allow the longitudinal follow-up of patient, identification and tracing of those lost to follow-up.

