***Facility baseline evaluations:***

We will conduct baseline facility evaluations that will include:

1. Health facility assessment on the level of staffing with different health care cadres, equipment and supplies, and availability of guidelines relevant for diabetes care
2. A context assessment to assess the opinion and views of facility health care workers regarding facilities in their working environment

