|  | Study informed consent |  | X |  |  |  |
|  |  |  |  |  |  |  |
| **II. Enrollment & Study ID** | Study ID number assignment |  | X |  |  |  |
|  | Patient registration in Register |  | X |  |  |  |
|  | Patient file creation |  | X |  |  |  |
|  | Patient appointment card |  | X |  |  |  |
|  |  |  |  |  |  |  |
| **III. Physical Measurements** | Height |  | X |  |  |  |
|  | Weight |  | X | X | X | X |
|  | Waist circumference |  | X |  | X | X |
|  | Blood pressure |  | X | X | X | X |
|  | 7-day pedometer steps |  | X |  |  | X |
|  |  |  |  |  |  |  |
| **IV. Biochemical** | FPG (Uganda & South Africa) | X, X | X | X | X | X |
|  | HbA1c (All sites) |  | X |  |  | X |
|  |  |  |  |  |  |  |
| **V. Basic participant data** | Pre-eligibility assessment | X |  |  |  |  |
|  | Eligibility confirmation |  | X |  |  |  |
|  | Eligibility and recruitment check |  | X |  |  |  |
|  | Contact Information |  | X |  |  |  |
|  | Demographic and social measures |  | X |  |  |  |
|  | Medical and medication history |  | X |  |  |  |
|  | Behavioral measures (diet, physical activity, foot care, tobacco use, alcohol consumption) |  | X |  |  | X |
|  |  |  |  |  |  |  |
| **VI. Intervention process measures** | Participant diabetes knowledge |  | X |  |  | X |
|  | Illness perception |  | X |  |  | X |
|  | Social support and sources of support |  | X |  |  | X |
|  | Self-efficacy, autonomy support & self-regulation |  | X |  |  | X |
|  | Psychological adjustment |  | X |  |  | X |
|  | Quality of life & Stress |  | X |  |  | X |
|  | Diabetes treatment satisfaction |  |  |  |  | X |
|  | Out of pocket expenditure |  |  | X | X | X |
|  | Incremental cost to the health facility |  |  | X | X | X |
|  | Adherence to study procedures and to intervention elements |  | X |  |  | X |
|  |  |  |  |  |  |  |
| **VII. Facility forms** | Process evaluation |  |  | X | X | X |
|  |  |  |  |  |  |  |
| **VIII. Community forms** | Environment context measurement (EPOC) |  | X |  |  |  |

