j) Differences between the country sites, and changes within these contexts, as a result of implementing the intervention elements.

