### 3.13.2 Analyses of secondary objectives

1. For the "incidence of progression from pre-diabetes state to diabetes state", we will use Kaplan Meier methods to compare incidence between the two arms. The log-rank test will be used and Kaplan-Meier curves will be plotted for each treatment group.
2. Adverse events, including hospitalizations due to hypo- or hyperglycemia, morbidity. For adverse events outcomes, we must account for the possibility that participants may experience multiple episodes over the study period. Thus, we will use log-binomial models for repeated outcomes to examine the treatment effect on these outcomes
3. For costs outcomes, cost evaluation will be undertaken from the health program provider perspective. The health service use costs of the two strategies will be calculated at 12 months in both arms. Costs incurred between baseline and 12 months will be discounted at ??%. The mean cost of the two groups over 12 months will be compared using non-parametric tests. Results will be reported with 95% confidence intervals and uncertainty will be examined using sensitivity analysis. An incremental cost-effectiveness ratio will be calculated over the 12 months of the intervention. The need or otherwise for cost-effectiveness modeling will depend on there being economically important clinically significant differences in glycaemic control, as determined by the likely impact on and hence, long-term effects on morbidity and mortality. Whether any differences in glycaemic control are important will be informed by reviewing the cost-effectiveness of other interventions that have been evaluated using lifetime models. If such differences do exist, the modeling of the longer-term effects to assess the incremental cost per quality adjusted life-year will be conducted
4. For comparison of differences between the country sites, in regard to baseline context infrastructure situation for prevention and management of diabetes, these are baseline comparisons thus for continuous context variables, we will use the t-test statistic or the equivalent non-parametric test. For categorical context variables we will use the chi-square test statistic.

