5. Similarly, for the degree of implementation of the intervention elements in each country, and differences between the country sites, we will compare the process evaluation variables/ indicators regarding ways in which program services and goods are provided (i.e. deviations) using the t-test statistic or the equivalent non-parametric test. For categorical context variables we will use the chi-square test statistic.
6. To compare changes in participant perceptions towards diabetes, physical activity, dietary behavior; and changes within contexts, as a result of implementing the intervention elements; we use multivariable linear regression mixed effects modeling with a random intercept, unstructured correlation matrix and robust standard errors, to evaluate changes over time in these outcomes of interest in relation to the assigned study arm. Visit month (categorical) at which the outcome is measured, study arm would be included in the model as fixed effects. The null hypothesis to be tested in this analysis would be that the mean changes at all the post-baseline visit months are equal between the treatment groups. The alternative hypothesis would be that the mean changes are not equal at, at least one post-baseline visit month.

We recognize that since sample size calculations for this trial were not based on the secondary outcomes, lack of significant differences in analysis of secondary outcomes might either be true lack of differences in these outcomes, or due to the fact that the trial was not sufficiently powered to detect differences in these outcomes. Thus interpretation of findings on secondary outcomes will be done with caution in case we do not detect any differences.

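### The protocol and its data collection tools time the facility and community context measures differently, and neither schedule gives those measures a baseline and follow-up pair

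*Protocol*

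**What the plan says.** Secondary objective 2 is "To evaluate differences between the country sites, in regard to baseline context infrastructure situation for prevention and management of diabetes". Section 3.9(g) lists the matching outcome, and section 3.13.2 item 4 gives the analysis: "these are baseline comparisons thus for continuous context variables, we will use the t-test statistic".

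Section 3.9(j) adds a further outcome: "Differences between the country sites, and changes within these contexts, as a result of implementing the intervention elements". Section 3.13.2 item 6 covers "changes within contexts, as a result of implementing the intervention elements" with a mixed model by study arm. Its null hypothesis is equal mean change across arms at every post-baseline visit.

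The timing is given in three places:

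- Section 3.7 states: "We will conduct baseline facility evaluations that will include" an assessment of staffing, equipment, supplies and guidelines. It also makes the community environment evaluation part of baseline.
- Table 15 (section 3.8) marks the community row at the baseline visit only. It has no row for the facility assessment.
- Table 3 of the data collection tools (Part III) has a row "Health facility survey – to be administered to head of health facility" and a row for EPOCH. Both are marked under months 2 to 11 only, with the baseline and end-line columns empty. A note says that neither tool is included in the set.

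On facility care, section 3.3.2.1 says of the minimum quality elements: "Should key elements be missing, they will be implemented as part of the trial".

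**The concern.** The facility assessment covers things that the trial itself supplies. A reading taken after supply describes the intervention, not the context that the trial found. Which schedule the sites follow therefore decides whether objective 2 is answered with pre-intervention data. The risk is uneven across countries, because most of the supply goes to Uganda, so it would bear directly on a comparison between countries.

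The second problem does not depend on which schedule wins. An analysis of change from baseline needs a baseline reading and at least one later reading of the same measure.

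**Working it through.** No sample-size or power figure is involved. The check sets the schedules side by side and counts time points.

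**Step 1. Planned time points**

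| Measure | Section 3.7 | Table 15 | Tool Table 3 | Baseline and follow-up pair |
|---|---|---|---|---|
| Facility assessment / survey | Baseline | No row | Months 2–11 only | None |
| EPOC(H) | Baseline | Baseline only | Months 2–11 only | None |
| Facility process evaluation | Not listed | Months 3, 6, 12 | Not listed | None (no baseline) |

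**Step 2. Could the months 2–11 mark include baseline?** This is unlikely. Table 1 of the same tools marks fasting glucose under both baseline and months 2–11, so the baseline column is ticked when a baseline reading is meant.

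**Step 3. What would a reading at months 2–11 capture?** Section 3.3.2.3 says that in Uganda the infrastructure is inadequate, guidelines are not implemented and an information system is lacking, and that the intervention will provide all three. Table 5 lists seven equipment and medicine items supplied by the trial in Uganda: glucometers and strips, HbA1c analyser and kits, blood pressure machines, scales, stadiometers, tapes, and stock-out medicines. In South Africa and Sweden the listed equipment is pre-existing and only standardised.

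Uganda has 9 facilities and three arms, one of them current practice. The number of facilities per arm is not stated. With c current-practice facilities, the number receiving the facility strategy is 9 − c:

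- c = 3 (equal split, assumed): 9 − 3 = 6
- c = 2: 9 − 2 = 7
- c = 4: 9 − 4 = 5

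So roughly 5 to 7 of the 9 Ugandan facilities would be surveyed after supply if tool Table 3 were followed.

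**Step 4. Is the word baseline enough?** The baseline column of Table 15 is a participant visit. The planned timeline puts equipment acquisition in June to September 2016, staff training in August and September 2016, and pilot implementation in October 2016. Enrolment starts in January 2017. Acquisition is not installation, but a facility reading tied only to enrolment could still fall after supply. The anchor has to be the cluster, before trial inputs arrive.

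**Step 5. Change.** Item 6 tests mean change at post-baseline visits. Under section 3.7 and Table 15 there is a baseline and no later reading. Under tool Table 3 there is no baseline. The number of planned pairs is 0 for both tools under both schedules.

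**The case against.** The strongest reply is that the protocol body is clear and nothing says the tools override it. Section 3.7 schedules both measures at baseline, Table 15 agrees for EPOC, and item 4 treats them as baseline data. This stands. A reader might infer that baseline context differences cannot be estimated at all; the document does not support that. They are at risk only where sites work from tool Table 3.

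A second reply is that the health facility survey in tool Table 3 is nowhere said to be the assessment in section 3.7, and its content is not shown. This also stands. That the survey would record trial-supplied items is an inference. It is strongest for Uganda's intervention facilities, weak for South Africa and Sweden, and does not apply to the Ugandan current-practice arm. If the two instruments are different, however, the baseline facility assessment has no row in either schedule table.

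Third, the pre-trial state would not be wholly lost. Section 3.3.2.1 plans a review of present care before missing elements are added, and Table 5 separates pre-existing from trial-supplied items by country.

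Fourth, a reader might infer that no change in context can be studied. That goes too far. Process evaluation runs at months 3, 6 and 12, Part III of the tools plans narratives on the socio-political climate over time, and neither 3.9(j) nor item 6 names EPOCH. The figure that maps context aspects to tools is not available here. What remains is narrower: the process evaluation has no baseline, and EPOCH and the facility assessment have no planned pair.

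Finally, a mark under months 2–11 is a window, and a site that followed both schedules would have two EPOCH readings. That would be an accident of the contradiction; no schedule plans it.

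**Conclusion.** The contradiction is real and should be resolved. It puts objective 2, outcome 3.9(g) and analysis item 4 at risk only if sites follow tool Table 3. In that case about 6 of 9 Ugandan facilities (5 to 7 over the range shown) would probably be read after supply. This assumes that the survey covers what section 3.7 describes and that supply precedes month 2. Under section 3.7 the baseline comparison remains estimable.

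The second part holds under either schedule: outcome 3.9(j) and analysis item 6 cannot estimate change from baseline with EPOCH or the facility assessment. Both parts concern secondary, largely descriptive context outcomes and leave the HbA1c outcomes untouched. The point still merits correction, because a reading missed before supply can be only partly reconstructed and the change costs little.

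**What to change.** 1. In Table 3 of the data collection tools, move the health facility survey and EPOCH to baseline, so that the table agrees with section 3.7 and Table 15. State whether the survey is the section 3.7 facility assessment.
2. State that both are completed in each cluster before any trial-supplied equipment, guidelines, training or community mobilisation begins there.
3. Add a row for the facility assessment to Table 15.
4. For 3.9(j) and analysis item 6, choose one of two options. Either limit them to context measures that are actually repeated, or repeat the brief head-of-facility questionnaire at month 12, alongside the process evaluation already scheduled then. If EPOCH is not repeated, say that it contributes to baseline description only.

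Items 1 to 3 are edits to tables and text, though item 2 also fixes when the fieldwork must be done. The repeat option in item 4 costs one extra questionnaire per facility, or 9 + 2 + 4 = 15 by the cluster counts in section 3.10. Narrowing the outcome costs nothing in the field.
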